## AMENDMENT HISTORY

| Amendment No. | Protocol Version No. | Date issued | Author(s) of changes | Details of Changes made                                       |
|---------------|----------------------|-------------|----------------------|---------------------------------------------------------------|
| 1             | 1                    | 5/9/2018    | [name]            | First draft                                                   |
| 2             | 1.1                  | 28/9/2018   | [name]            | Sample size, inclusion criteria, data collection and analysis |
| 3             | 1.2                  | 4/1/2019    | [name]            | Specified data retention period                               |

List details of all protocol amendments here whenever a new version of the protocol is produced.

**SYNOPSIS**

|                                            |                                                                                                                                                                                                                                                                                                                                                                                                                                                                                                                                                                                                                                                                                                                                                                                                                                                                                                                                                                                                                                                                                                                                                                                                                                                                                                                                                                                                                                                                                                                                                                                                                                                                  |
|--------------------------------------------|------------------------------------------------------------------------------------------------------------------------------------------------------------------------------------------------------------------------------------------------------------------------------------------------------------------------------------------------------------------------------------------------------------------------------------------------------------------------------------------------------------------------------------------------------------------------------------------------------------------------------------------------------------------------------------------------------------------------------------------------------------------------------------------------------------------------------------------------------------------------------------------------------------------------------------------------------------------------------------------------------------------------------------------------------------------------------------------------------------------------------------------------------------------------------------------------------------------------------------------------------------------------------------------------------------------------------------------------------------------------------------------------------------------------------------------------------------------------------------------------------------------------------------------------------------------------------------------------------------------------------------------------------------------|
| Study Title                         | Selective brain temperature management after traumatic brain injury – SELETherm                                                                                                                                                                                                                                                                                                                                                                                                                                                                                                                                                                                                                                                                                                                                                                                                                                                                                                                                                                                                                                                                                                                                                                                                                                                                                                                                                                                                                                                                                                                                                                                  |
| Internal ref. no.                   | ALEG - 01                                                                                                                                                                                                                                                                                                                                                                                                                                                                                                                                                                                                                                                                                                                                                                                                                                                                                                                                                                                                                                                                                                                                                                                                                                                                                                                                                                                                                                                                                                                                                                                                                                                        |
| Study Design                        | 
Interventional, randomised, first-in-human, proof-of-concept pilot study comparing two methods of brain temperature management following brain injury: total body cooling (standard care) and selective cervical cooling (experimental).
 
Target temperature management delivered by means of systemic cooling is standard of care for brain protection following severe TBI. This is typically delivered by means of body surface cooling and infusion of ice-cold crystalloids. Systemic cooling is known to be associated with cardiac, respiratory, renal and infective complications.
 
This study will test the feasibility and safety of cervical cooling to deliver selective brain cooling in a small number of brain injured patients – as instigated by the NIHR i4i panel.
 
Brain temperature and systemic temperature will be monitored as part of standard clinical care. Temperature management will be delivered by means of standard care (systemic cooling) or by selective cervical cooling using a purpose-built prototype, developed and provided by Neuronguard.
 
The primary outcomes will be safety of the experimental strategy, its ability to maintain brain temperature within temperature targets set by the treating physician and the proof-of-concept that cervical cooling can induce selective brain cooling (i.e. quantified as the brain-body temperature gradient).
 
If cervical cooling shows the ability to deliver selective brain temperature, the strategy will be tested in subsequent clinical study on a larger sample to describe its safety profile against systemic cooling.
 |
| Study Participants                  | Adult, comatose patients admitted to NCCU with acute brain injury as a result of brain trauma with clinical indication for invasive monitoring of brain physiology (i.e. intracranial pressure, cerebral oximetry and parenchymal brain temperature, cerebral microdialysis) as part of their standard clinical management and indication for target temperature management at temperature target < 35 C. Patients with devastating injuries not expected to survive 24 hours will be excluded from the study.                                                                                                                                                                                                                                                                                                                                                                                                                                                                                                                                                                                                                                                                                                                                                                                                                                                                                                                                                                                                                                                                                                                                                   |
| Planned Sample Size (if applicable) | 
At least 10 patients will be randomly allocated to two groups using pre-allocated sealed identical envelopes.
 
Standard care (5 patients): standard clinical protocol;
                                                                                                                                                                                                                                                                                                                                                                                                                                                                                                                                                                                                                                                                                                                                                                                                                                                                                                                                                                                                                                                                                                                                                                                                                                                                                                                                                                                                                                                                       |

|                             |                                                                                                                                                                                                                                                                                                                                                                                                                                                                                                                     |
|-----------------------------|---------------------------------------------------------------------------------------------------------------------------------------------------------------------------------------------------------------------------------------------------------------------------------------------------------------------------------------------------------------------------------------------------------------------------------------------------------------------------------------------------------------------|
|                             | Experimental care (5 patients): standard clinical care with cervical cooling and systemic cooling allowed as a rescue procedure if temperature targets not achieved;                                                                                                                                                                                                                                                                                                                                         |
| Planned Study Period | 90 days – the trial will be interrupted early if there is any concern regarding the safety of the device.                                                                                                                                                                                                                                                                                                                                                                                                           |
| Primary Objective    | 
Safety. Describe number and severity of complications associated with induction and of hypothermia using selective cervical cooling:
 
 
• failure to maintain the brain within target temperature;
 
• number of instances where external cooling blankets or ice-cold saline had to be used as a rescue strategy to achieve target temperature;
 
• duration and severity of cerebral hyperthermia;
 
• any other adverse event;
 
 |
| Secondary Objectives | 
Proof of concept. Describe the ability of the device to deliver selective brain cooling, and its effectiveness:
 
 
• differential brain-to-core temperature as evidence of selective cooling (between-group comparison);
 
• brain temperature within target parameters (between-group comparison);
 
                                                                                                                                             |
|                             |                                                                                                                                                                                                                                                                                                                                                                                                                                                                                                                     |

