## 1. BACKGROUND AND RATIONALE

Targeted temperature management is the standard of care for patients with acute neurological injuries, with level I evidence supporting its use following out of hospital cardiac arrest. The benefits of therapeutic hypothermia in brain injuries associated with trauma, haemorrhage or embolic events remains to be conclusively demonstrated.

It is undisputed that despite the neuroprotective effects of hypothermia, the induction and maintenance of systemic hypothermia is associated with side effects in clinical practice. A recent trial (Eurotherm3235) provides evidence against therapeutic hypothermia as an early measure to lower intracranial pressure [1]. Although the study provides no guidance on the use of therapeutic hypothermia for refractory intracranial hypertension, the findings of the Eurotherm trial raised concerns in regards to whether the risks of therapeutic hypothermia may outweigh its benefits even in patients with refractory intracranial hypertension. It is our opinion that therapeutic hypothermia should remain part of standard clinical protocols for patients with acute brain injuries and intracranial hypertension refractory to “level I” options [2].

Cervical temperature management may provide the benefits of hypothermic or normothermic neuroprotection without the renal, cardiac and infectious side effects of systemic hypothermia. This is a preliminary, **proof-of-concept investigation aiming to demonstrate that cervical cooling can safely induce selective brain cooling**. The study was instigated by the NIHR i4i panel, in consideration of a larger clinical trial of selective brain cooling following severe traumatic brain injury.

Our group previously conducted a preclinical study on large animals (sheep) with a neck cooling prototype, demonstrating that a differential reduction between the brain and body temperature could be induced by cooling the neck of the animal [3]. The prototype was also tested on healthy human subjects as part of the development process. In standard conditions (room temperature 23°C, supine resting position) we observed a reduction of tympanic temperature of 1°C, achieved over a period of one hour, followed by the onset of shivering. Testing the strategy in healthy subjects is clearly limited due to the lack of invasive brain temperature monitoring and for limited tolerance to hypothermia in non-sedated patients.

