## 2. OBJECTIVES

### 2.1 Primary Objective

**Safety.** Describe number and severity of complications associated with induction and maintenance of hypothermia using selective cervical cooling:

- failure to maintain the brain within target temperature;
- number of instances where external cooling blankets or ice-cold saline had to be used as a rescue strategy to achieve target temperature;
- duration and severity of cerebral hyperthermia;
- any other adverse event;

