## 3. STUDY DESIGN

This is a preliminary, proof-of-concept, randomised, interventional study.

The study will enrol at least 10 patients admitted to the Neurosciences and Trauma Critical Care Unit (NCCU, Addenbrooke's) following severe traumatic brain injury requiring invasive brain temperature monitoring and target temperature management as standard of care.

Brain temperature monitoring includes: ICP, brain oxymetry, microdialysis, haemodynamic variables. Physiological parameters and blood tests are also sampled on the ICM+ platform and local electronic medical record systems.

Randomisation of at least 10 patients will be made after the treating clinician has set a target temperature of 35°C. Using predetermined identical envelopes, patients will be assigned to two groups:

**Group 1, Standard Care (5 patients):** Medical and surgical management as per local treatment protocol (Figure). **Targeted temperature management induced by rapid infusion of ice-cold saline and maintained by automated cooling blankets.**

**Group 2, Experimental Care (5 patients):** Patients allocated to group 2 will receive the same treatment as those in group 1, with the exception of maintenance of **target temperature by using selective cervical cooling.**

Cervical cooling will be delivered with a purpose built prototype developed by Neuronguard. Brain temperature, core temperature (bladder or oesophageal), ICP and other physiological parameters will be continuously monitored and captured digitally as per standard local practice. Temperature targets are determined by the treating clinician, they will be recorded by a chart at the bedside, updated hourly, with brain temperature targets expressed as absolute values  $\pm 0.5^{\circ}\text{C}$ . Monitoring will continue for 48 hours, irrespective of temperature targets (i.e. to include rewarming, if indicated).

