### 4.2 Study Assessments/Interventions

| Intervention or procedure                                | Total number of interventions/procedures received by each participant | Who will conduct the intervention/procedure |
|----------------------------------------------------------|-----------------------------------------------------------------------|---------------------------------------------|
| Randomisation                                            | 1                                                                     | Principal Investigator / LT                 |
| Selective Brain Cooling using the Neuronguard device     | 1                                                                     | Principal Investigator / LT                 |
| Off-line review of medical data and records for analysis | 1                                                                     | Principal Investigator / LT                 |

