#### 6.3 Analysis of Endpoints

Descriptive statistics will be used to report demographics and rate and nature of adverse events.

Non parametric tests will be used for between-group comparison of temperature data and paired data non parametric statistic tests for the brain/body differential temperature analysis.

Further exploratory data analysis of association between brain physiology, brain temperature, brain-body temperature gradients will be performed in the two groups to generate hypotheses for a larger clinical trial.

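### The systemic harms that motivate the device have no item of their own in the primary safety objective, so non-serious ones can rest on unblinded judgement

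*Protocol*

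**What the plan says.** **Harms that motivate the device.** The Synopsis (Study Design) says that "Systemic cooling is known to be associated with cardiac, respiratory, renal and infective complications". Section 1 presents cervical cooling as possibly protective "without the renal, cardiac and infectious side effects of systemic hypothermia". Respiratory harm appears only in the first of these, as a harm of systemic cooling.

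**Primary objective.** Section 2.1 reads: "Describe number and severity of complications associated with induction and maintenance of hypothermia using selective cervical cooling". Three of its four items concern failure to hold the brain at target, use of rescue cooling, and cerebral hyperthermia. The fourth is "any other adverse event".

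**What will be reported.** The end of section 1 promises the type and frequency of side effects or complications. Section 6.3 says: "Descriptive statistics will be used to report demographics and rate and nature of adverse events".

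**Who does what.** The procedures table in section 4.2 (Study Assessments/Interventions) lists three tasks: randomisation, "Selective Brain Cooling using the Neuronguard device" and "Off-line review of medical data and records for analysis". All three carry the same role entry, headed by the Principal Investigator.

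**Data held.** Section 3 lists haemodynamic variables among what is monitored and adds: "Physiological parameters and blood tests are also sampled on the ICM+ platform and local electronic medical record systems".

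**The concern.** Safety is the primary objective, and the case for the device is that it may avoid certain systemic harms. One would expect those harms to be counted by a stated rule in both arms. Instead they are left to an open item. In sedated intensive-care patients, whether a rhythm disturbance or a creatinine rise counts as an adverse event or as the expected course is a judgement, and the protocol describes nobody making it without knowledge of the arm. A reviewer who expects systemic harm under body cooling may note more of it there. One who is watchful over a new device may note more of it in the device arm. At stake is whether the adverse-event table describes the patients or the reviewer's threshold.

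**Working it through.** The protocol gives no event rate, margin or sample size calculation, so it has no figure of its own to reproduce. The check is mainly a reading of the sections side by side.

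**1. Where each harm can be counted**

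| Harm | Named as a motive | Own item in 2.1 | Other route |
|---|---|---|---|
| Cardiac | Synopsis, section 1 | No | 5.1 if serious; otherwise open item |
| Renal | Synopsis, section 1 | No | 5.1 if serious; otherwise open item |
| Infective | Synopsis, section 1 | No | 5.1 if serious; otherwise open item |
| Respiratory | Synopsis only, as a harm of systemic cooling | No | 5.1 if serious; otherwise open item |
| Neck skin lesion | Not a motive | No | Repeated nurse check (section 7) |

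The gap is therefore non-serious systemic events. Section 5.2 does not fill it: it governs which serious events go to the ethics committee, according to the Chief Investigator's opinion, and not which events are counted. The one structured harm check, of the neck skin, concerns a local harm.

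**2. Who ascertains.** No masked assessor or adjudication appears anywhere. Whoever randomises and fits a neck device knows the arm, and the same role entry reviews the records. Section 3 confirms that objective data are stored, but no rule turns them into events.

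**3. Granularity.** With 5 patients per arm (Synopsis, section 3), one patient classified differently moves an arm's rate by 1/5 = 20 percentage points.

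**4. Illustration only.** The rates and recording fractions below are assumptions. Let the true harm rate p be equal in both arms, with every control event recorded and a fraction s of device-arm events recorded. The recorded rates are p and p × s. The chance that control shows more affected patients is the sum, over all c > e, of Bin(c; 5, p) × Bin(e; 5, p × s).

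| True rate p | s | Recorded, control v device | P(control more) | P(device more) |
|---|---|---|---|---|
| 20% | 100% | 20% v 20% | 0.340 | 0.340 |
| 20% | 80% | 20% v 16% | 0.395 | 0.272 |
| 20% | 60% | 20% v 12% | 0.455 | 0.204 |
| 40% | 100% | 40% v 40% | 0.374 | 0.374 |
| 40% | 80% | 40% v 32% | 0.477 | 0.274 |
| 40% | 60% | 40% v 24% | 0.587 | 0.183 |
| 60% | 100% | 60% v 60% | 0.374 | 0.374 |
| 60% | 80% | 60% v 48% | 0.530 | 0.240 |
| 60% | 60% | 60% v 36% | 0.682 | 0.135 |

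If the under-recording is in the control arm instead, the last two columns swap. The direction of any bias is therefore not known in advance.

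**5. What five per arm can show even with perfect recording.** Zero events in 5 leaves a one-sided 95% upper limit of 1 − 0.05^(1/5) = 0.451. Fisher's exact test gives p = 110/210 = 0.52 for 3/5 v 1/5, and needs 4/5 v 0/5 to reach p = 0.048. The harm table can describe; it cannot support a conclusion about a difference.

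**The case against.** Much of the case on the other side stands.

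- **A planned safety comparison.** A reader might infer that the trial sets out to compare harms between arms. It does not. Section 2.1 is worded for cervical cooling, only the temperature items in 2.2 are labelled as between-group, section 6.3 is descriptive for adverse events, and the Synopsis leaves the safety profile against systemic cooling to a later, larger study.
- **The larger trial resting on these rates.** This too might be inferred. The Synopsis makes the next study depend on showing selective brain cooling. Section 6.1 says the funder wanted safety and feasibility assessed first, but gives no role to a difference in harm rates.
- **Adverse events drawn only from the off-line review, by the person who fitted the device.** The procedures table does not say so, and the role entry may cover two people. It is, however, the only record-review step listed, no other way of finding systemic harms is given, and nobody independent of treatment is named.
- **No criteria at all.** Section 5.1 has criteria for serious events, and serious systemic harms would meet them.
- **Respiratory harm spared by the device.** No section claims this.
- **An open item suits a first-in-human device, and detailed thresholds often sit in an analysis plan or case report form.** Both are true, and the open item should stay. But which harms are primary safety items, and who ascertains them, is fixed in the protocol. A later plan cannot undo judgement already exercised at collection.
- **Objective items cannot isolate the device's effect.** This stands. Read literally, section 3 makes Group 2 differ from Group 1 only in how temperature is maintained, and the Synopsis and section 7 allow systemic rescue. Device patients may thus receive systemic cooling. That is a reason to record it beside the harms, and a reason not to presume such harms absent in that arm.

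**Conclusion.** The point holds in a limited form. Under the plan as written, non-serious cardiac, renal, infective and respiratory events in a primary safety objective are counted at unblinded discretion, although sections 1 and 6.3 promise their frequency or rate. The consequence is a descriptive adverse-event table by arm that may be biased in either direction, not a false formal inference.

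The size cannot be derived from the documents. The only firm figure is the 20-point step per patient; the table of chances rests entirely on assumed rates and recording fractions. The conclusion assumes that those who randomise and apply the device know the arm, which no section contradicts, and that no other ascertainment route exists beyond those described. No change in sample size follows. The change is worth making because a less biased method is available at little cost from data the protocol says are stored.

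**What to change.** In section 2.1 (and the matching Synopsis row), add a short list of systemic harm items:

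- At minimum a cardiac and a renal item, each scored by a threshold fixed before the first patient, on the haemodynamic variables and blood tests that section 3 says are captured.
- A respiratory item and a microbiology-based infective item where those records are held. The protocol does not name blood-gas, ventilator or microbiology data, so this should be confirmed first.
- Infective events labelled as early, since monitoring ends at 48 hours. A new antibiotic course should not be the sole criterion, because starting one is itself an unblinded decision.
- Extraction by the same rule for all randomised patients, reported descriptively by arm, with any systemic cooling received in the device arm shown alongside.
- The existing open item kept as free text for unforeseen events.

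The cost is agreeing the definitions and running one common extraction. For the cardiac and renal items, no extra patients or measurements are needed.
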